### **9.3.5. Chest X-ray\***

Chest X-rays (preferably both posteroanterior and lateral views) will be obtained according to the Time and Events Schedule, and at any other time deemed appropriate by the investigator. Chest X-rays should be interpreted by the investigator, a pulmonologist, or radiologist and interpreted with respect to the baseline chest X-ray for clinical management of the subject during the study. Chest X-rays obtained from the predose and TOC visits will be interpreted at a central location. The chest x-rays will be centrally read to confirm the presence of a qualifying infiltrate at baseline and to confirm the site interpretation at TOC.

## **9.4. Efficacy Criteria**

### **Primary Endpoint**

The clinical cure rate is defined as the ratio of the number of clinically cured subjects to the total number of subjects in the population at the TOC visit.

### **Secondary Endpoints**

- Microbiological eradication rate at TOC visit
- Clinical cure rate in subjects requiring mechanical ventilation within 48 hours of enrollment
- Microbiological cure rate in subjects requiring mechanical ventilation within 48 hours of enrollment

---

\* This section of the protocol has been revised. Please refer to the section of this document entitled PROTOCOL AMENDMENTS (Amendment INT-3, 22 December 2006) for a detailed description of the specific changes.

- Clinical and microbiological relapse at LFU visit
- Thirty-day pneumonia-specific mortality rates (all deaths due to pneumonia within 30 days after randomization).

For the definition of these parameters see Section 11.4.2, Definition of Parameters.

9.5. Safety Evaluations\*

The study will include the following evaluations of safety and tolerability (refer to Time and Events Schedule for when these assessments are to be completed):

- **Adverse Events**  
Adverse events will be reported by the subject (or, when appropriate, by a caregiver, surrogate, or the subject’s legally acceptable representative) for the duration of the study. Adverse events will be followed by the investigator for a length of time as determined by the sponsor. Specific details on adverse event reporting are provided in Section 12.
- **Clinical Laboratory Tests**  
Blood samples will be collected for serum chemistry and hematology and a random urine sample will be collected for urinalysis. The investigator must review the laboratory report, document this review, and record any clinically relevant changes occurring during the study in the adverse event section of the CRF. The following tests will be performed by the central laboratory:

Hematology Panel

|                             |                |
|-----------------------------|----------------|
| hemoglobin                  | ANC            |
| hematocrit                  | platelet count |
| red blood cell (RBC) count  |                |
| WBC count with differential |                |

Subjects with moderate anemia (hemoglobin between 6.5 and 7.9 g/dL) or moderate thrombocytopenia (50.0 to 74.9 x 10^9/cm) should have a complete blood count performed at least every other day.

\* This section of the protocol has been revised. Please refer to the section of this document entitled PROTOCOL AMENDMENTS (Amendment INT-3, 22 December 2006) for a detailed description of the specific changes.

Serum Chemistry Panel

|                                 |                             |
|---------------------------------|-----------------------------|
| sodium                          | alkaline phosphatase        |
| potassium                       | creatinine phosphokinase    |
| urea                            | lactate dehydrogenase (LDH) |
| bicarbonate                     | uric acid                   |
| AST                             | calcium                     |
| ALT                             | triglycerides               |
| glucose                         | albumin                     |
| gamma glutamyltransferase (GGT) | total protein               |
| total bilirubin                 | cholesterol                 |
| serum creatinine                | chloride                    |

Serum for Mycoplasma pneumoniae and Chlamydia pneumoniae antibody titers

Creatinine clearance will be estimated by use of the Cockcroft and Gault equation.

Men:  $Cl_{Cr} \text{ (mL/min)} = \text{Weight (kg)} \times (140 - \text{age in years}) / 72 \times \text{serum creatinine (mg/dL)}$

Women: 0.85 x above value

To convert serum creatinine in mol/L to mg/dL divide by 88.4.

Additional tests of liver function will be performed if indicated.

Subjects with serum sodium levels outside of the normal range at baseline or during the study should have their electrolytes measured on a daily basis or more often as clinically indicated until the serum sodium level is within the normal range.

Urinalysis

|                  |                  |
|------------------|------------------|
| Dipstick  | Sediment* |
| specific gravity | RBC              |
| pH               | WBC              |
| glucose          | epithelial cells |
| protein          | crystals         |
| blood            | casts            |
| ketones          | bacteria         |
| bilirubin        |                  |
| urobilinogen     |                  |
| nitrite          |                  |

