## JNJ-30982081: Clinical Protocol 30982081-CAP-3001 - Amendment INT-3

- History of or suspected condition that may jeopardize adherence to protocol requirements (e.g., severe cardiac disease such that even minimal physical activity causes discomfort, New York Heart Association [NYHA] Class 4)
- History of or suspected hypersensitivity to any related anti-infective (including beta-lactam antibiotics such as penicillins and cephalosporins, oxazolidinones). Subjects in whom cephalosporins would be used as part of normal clinical practice are not excluded.
- History of or suspected condition or concurrent treatment that would be contraindicated by the prescribing information for ceftriaxone or linezolid
- History of or suspected severe renal impairment, (i.e.,  $Cl_{Cr} \leq 30$  mL/min or oliguria  $<20$  mL/h unresponsive to fluid challenge) or any form of dialysis
- History of or suspected hepatic dysfunction (total bilirubin, or alanine aminotransferase [ALT], or aspartate aminotransferase [AST]  $\geq 3$  times the upper limit of the normal range [ULN]).
- History of suspected extra-pulmonary infection, including concomitant meningitis, endocarditis, septic arthritis, or osteomyelitis
- Known to be human immunodeficiency virus (HIV) positive with CD4 counts of  $\leq 0.2 \times 10^9/L$  ( $\leq 200$  cells/mm^3). (Subjects with HIV and  $>0.2 \times 10^9/L$  [ $>200$  cells/mm^3] may be included)
- Presence of neutropenia, (absolute neutrophil count [ANC]  $\leq 0.5 \times 10^9/L$  [ $<500$  Neutrophils [polymorphonuclear leukocytes] [PMNs/mm^3]) severe anemia (hemoglobin  $<6.5$  g/dL), or severe thrombocytopenia ( $<49.9 \times 10^9/cm$ ). *Note: Subjects receiving immunosuppressive therapy who are expected to reach a nadir of  $<500$  PMNs/mm^3 during administration of study drug should not be enrolled*
- Previous enrollment in this study or any other ceftobiprole protocol
- Have received an experimental drug or used an experimental medical device within 30 days before the planned start of treatment
- Is pregnant or breast-feeding
- Employees of the investigator or study center, with direct involvement in the proposed study or other studies under the direction of that investigator or study center, as well as family members of the employees or the investigator

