#### **6.1.4. Dose Adjustment for Renal Impairment**

Dose adjustment for renal impairment will be made according to  $Cl_{Cr}$  at enrollment and will be adjusted if there are any changes during the study. Additional assessments of serum creatinine or renal function may be performed at the local laboratory at any time during the study, as clinically indicated. NOTE: Although subjects with  $Cl_{Cr}$  of  $\leq 30$  mL/min are initially excluded, if a subject's  $Cl_{Cr}$  decreases to  $\leq 30$  mL/min after enrollment they may remain in the study and the dosage of study drug(s) should be changed accordingly. Placebo infusions should be added as needed to maintain the blind.

- Cefetobiprole: in subjects with moderate renal impairment ( $Cl_{Cr} > 30$  to  $\leq 50$  mL/min) cefetobiprole will be infused at a dose of 500 mg every 12 hours over 120 minutes. In subjects with severe renal impairment ( $Cl_{Cr} > 10$  to  $\leq 30$  mL/min) 250 mg of cefetobiprole will be infused every 12 hours over 120 minutes. Subjects whose  $Cl_{Cr}$  level falls to  $\leq 10$  mL/min are to be discontinued from the study.
- Ceftriaxone: No adjustment of ceftriaxone is recommended in subjects with renal impairment provided the daily dose is 2 g/day or less. To maintain the blind, subjects with  $Cl_{Cr} \leq 50$  mL/min, will receive placebo 2-hour infusions every 12 hours instead of every 8 hours.
- Linezolid: No adjustment is required.
- Cefuroxime axetil: Do not use in subjects with  $Cl_{Cr} < 30$  mL/min.

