### **10.2. Discontinuation of Treatment**

A subject should be discontinued from study treatment if:

- the investigator believes that for safety reasons (e.g., adverse event) it is in the best interest of the subject to stop treatment
- the subject becomes pregnant
- creatinine clearance is <10 mL/min or the subject requires dialysis
- significant myelosuppression occurs during therapy with linezolid/placebo; treatment with linezolid/placebo should be stopped unless it is considered absolutely necessary to continue therapy, in which case, intensive monitoring of blood counts and appropriate management strategies should be implemented
- optic or peripheral neuropathy occurs during therapy with linezolid/placebo; treatment with linezolid/placebo should be stopped

unless it is considered absolutely necessary to continue therapy. Optic and peripheral neuropathy are potential adverse effects of linezolid therapy. Subjects will be educated on symptoms associated with optic neuropathy (e.g., acute blurred vision, vision loss, color loss) and peripheral neuropathy (e.g., paresthesia, sensory loss) and instructed to report them if they occur. If subjects report symptoms of visual impairment, such as changes in visual acuity, changes in color vision, blurred vision, or visual field defect, prompt ophthalmic evaluation is recommended. Visual function should be monitored in all subjects reporting new visual symptoms, regardless of the length of linezolid therapy. Subjects with significant or progressive symptoms will be discontinued from linezolid/placebo therapy and referred for specialty evaluation if symptoms persist.

If a subject discontinues treatment early, TOC assessments should be performed at the time of study drug discontinuation. The subject should be contacted at the LFU visit to obtain MRU information and to follow up on any ongoing adverse events.

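### Section 9.5 prints the creatinine clearance formula without brackets round its denominator; applied literally, clearance rises with serum creatinine, against the protocol's own renal cut-offs

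*Protocol*

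**What the plan says.** Under Clinical Laboratory Tests, Section 9.5 fixes the method: "Creatinine clearance will be estimated by use of the Cockcroft and Gault equation". The next line gives the formula for men, on one line, as weight in kg multiplied by an expression that contains "140 - \text{age in years}) / 72 \times \text{serum creatinine (mg/dL". No bracket encloses the product of 72 and serum creatinine. Two short lines follow: "Women: 0.85 x above value" and "To convert serum creatinine in mol/L to mg/dL divide by 88.4". No other section prints a formula for creatinine clearance, and the amendment log lists no change to this one.

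The value is used elsewhere in the protocol:

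- Section 4.3 excludes subjects with "History of or suspected severe renal impairment", which it ties to a clearance of 30 mL/min or below, or to oliguria, and it also excludes any form of dialysis.
- Section 6.1.4 begins "Dose adjustment for renal impairment will be made according to" clearance at enrollment. It defines moderate impairment as above 30 up to 50 mL/min and severe impairment as above 10 up to 30. Subjects whose clearance falls to 10 or below "are to be discontinued from the study".
- Section 10.2 stops study treatment if "creatinine clearance is <10 mL/min or the subject requires dialysis".

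**The concern.** A protocol prints a formula so that sites and programmers do not have to work from memory. Evaluated as typed, left to right, this one puts creatinine in the numerator, so a subject with worsening renal function gets a rising clearance. Section 6.1.4 runs the other way: its categories move from moderate to severe to discontinuation as clearance falls. Section 1.1.1 agrees, reporting that ceftobiprole clearance tracked creatinine clearance in renally impaired subjects. The conflict is therefore internal to the protocol and does not depend on an outside source.

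The risk is one of transcription. Section 9.5 allows the chemistry used for eligibility, including renal function tests, to go to a local laboratory, and Section 6.1.4 allows creatinine to be repeated locally. A site that receives only a creatinine value has to calculate clearance, and this is the only formula it is given. If the line were copied unchanged into a worksheet or program, the entry criterion, the dose category and the stopping check would all be applied to a wrong number.

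**Working it through.** **Inputs from the protocol.** The printed line, the 0.85 factor for women and the cut-offs at 10, 30 and 50 mL/min. The protocol gives no worked clearance value to reproduce.

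**Assumed inputs.** The weights, ages and creatinine values below are illustrations and are not in the protocol.

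**Two readings.** Let W be weight in kg, A age in years and S serum creatinine in mg/dL.

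- Literal, left to right: W × (140 − A) / 72 × S
- Bracketed denominator: W × (140 − A) / (72 × S)

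Dividing the first by the second leaves S × S. The two readings agree only at S = 1.0 mg/dL. Above that the literal value is too high, and below it too low. The factor for women multiplies both readings and cancels from the ratio.

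**Numbers.** The base is W × (140 − A) / 72, times 0.85 for a woman.

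| Example subject | Base | S (mg/dL) | Literal = base × S | Bracketed = base / S | Category, literal | Category, bracketed |
|---|---|---|---|---|---|---|
| Man, 70 kg, 75 y | 70 × 65 / 72 = 63.2 | 2.5 | 158 | 25 | >50 | >10 to 30 |
| Man, 70 kg, 70 y | 70 × 70 / 72 = 68.1 | 2.0 | 136 | 34 | >50 | >30 to 50 |
| Man, 70 kg, 60 y | 70 × 80 / 72 = 77.8 | 1.0 | 77.8 | 77.8 | >50 | >50 |
| Man, 70 kg, 60 y | 77.8 | 8.0 | 622 | 9.7 | >50 | ≤10 |
| Woman, 55 kg, 75 y | 0.85 × 55 × 65 / 72 = 42.2 | 0.7 | 29.5 | 60 | >10 to 30 | >50 |

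The first man would be excluded under Section 4.3 on the bracketed value and pass on the literal one. The woman goes the other way. The fourth row falls below the stopping threshold only on the bracketed value.

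**Direction.** For the 70 kg man aged 60, the bracketed value falls from 77.8 at 1.0 mg/dL to 38.9 at 2.0, 25.9 at 3.0 and 9.7 at 8.0, passing through each of the protocol's categories in turn. The literal value rises over the same range: 77.8, 155.6, 233.3, 622.2. Only the bracketed reading fits Section 6.1.4.

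**The case against.** The strongest reply is that the method is fixed by name in the sentence just above the formula. Anyone who uses the named equation, or a laboratory that reports clearance by it, divides by creatinine. The literal result is also absurd on its face: a clearance of 622 mL/min at a creatinine of 8 mg/dL should stop any reader. This stands, and it limits the point to a defect in a printed rule. It does not remove the defect, because a transcribed formula carries no such judgement.

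A second reply is that the text was read from PDF, so a stacked fraction or lost brackets cannot be fully ruled out. The line reads as running text with a slash, which makes this less likely, but it should be checked against the source document. The same caution applies to the conversion line. The divisor 88.4 gives a usable result for micromol/L (265 / 88.4 = 3.0 mg/dL) and not for mol/L, but the prefix may have been lost in reading, so it is not counted here as an error.

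A third reply is that the exclusion does not rest on the formula alone: history or suspicion, oliguria and dialysis also count, and extra renal assessments are allowed. That is correct and gives some protection.

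Two stronger readings are tempting. A reader might infer that any exposure error would fall on the ceftobiprole arm alone. Section 6.1.4 does not support that: it also bars cefuroxime axetil, the oral switch in both arms, below 30 mL/min, and it changes the placebo infusion interval in the ceftriaxone arm at 50 mL/min or below. A reader might also infer that the renal covariate in the pharmacokinetic work would be reversed. Section 3.2 names renal function as a factor to explore, and Section 9.2.3 says the pooled analysis is reported separately. Neither ties the covariate to this line.

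**Conclusion.** The formula is wrong as printed and conflicts with the protocol's own use of creatinine clearance. If it is applied literally, the error is a factor of creatinine squared: about 6-fold at 2.5 mg/dL (2.5 × 2.5 = 6.25) and none at 1.0 mg/dL. That is enough to move the example subjects across the entry, dose-category and stopping cut-offs.

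The size is conditional on literal use. The example subjects are assumed, and the protocol gives no distribution of age, weight or creatinine from which to say how many subjects would change category. It would go too far to say that the cut-offs are in fact applied to wrong values: the equation is correctly named, no worksheet or program is shown, and no misclassification is documented. The correction should still be made, because the value governs eligibility, dosing and stopping.

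**What to change.** In Section 9.5, print: ClCr (mL/min) = [weight (kg) × (140 − age in years)] / [72 × serum creatinine (mg/dL)], with women at 0.85 times this value. Check the source document for the layout of the formula, and confirm that the conversion line reads micromol/L; correct it if it does not. Check any site worksheet, laboratory calculation or derivation program that uses the formula.

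No cut-off, category or dose is changed. While the text is open, Section 6.1.4 (discontinuation at 10 mL/min or below) and Section 10.2 (below 10 mL/min) should be reconciled, since they differ at exactly 10.

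The cost is one corrected line at the next amendment and a short check of existing tools.

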### leukocyte esterase

\*If positive dipstick results are obtained for blood or protein, a microscopic examination of sediment is required.

A urine or serum monoclonal antibody test for  $\beta$ -hCG must be performed at baseline and at the TOC visit for all women of childbearing potential. The result must be negative before first dosing of study drug. Additional serum or urine pregnancy tests will be conducted throughout the study in sufficient number, as determined by the investigator, to establish the absence of pregnancy during the study.

Note: Blood samples for WBC with differential and chemistries (electrolytes and renal and liver function tests) for evaluation of subject eligibility, as well as other samples deemed essential by the investigator for clinical management may be sent to the local laboratory, as necessary.

- **Electrocardiogram**

Twelve-lead ECGs will be recorded at a paper speed of 25 mm/sec so that the different ECG intervals (RR, PR, QRS, QT) can be measured.

- **Vital Signs** (temperature, pulse, respiratory rate, and blood pressure) must be measured twice daily at least 8 hours apart, while the subject is hospitalized (in addition to other time points listed in the Time and Events Schedule). The vital signs that reflect the highest temperature recorded for the subject on that day should be captured in the CRF.

- **Physical Examination**

Any clinically significant treatment-emergent abnormalities persisting at the end of the study will be followed by the investigator until resolution or until reaching a clinically stable endpoint.

### **Independent Data Monitoring Committee**

An IDMC will be established to monitor data on an ongoing basis to ensure the continuing safety of the subjects enrolled in this study and efficacy of the study drug. Thereafter, the committee will meet periodically to ensure continued safety and efficacy. After each review, the IDMC will make recommendations regarding the continuation of the study. The details will be provided in a separate IDMC charter.

The IDMC will consist of independent, multidisciplinary experts relevant to the study. The IDMC responsibilities, authorities, and procedures will be documented in its charter. Minutes of IDMC meetings will be provided to

the sponsor with comments and recommendations after the completion of the study in keeping with the established charter.

## **9.6. Medical Resource Utilization Data Collection**

During the study, and until completion of LFU, MRU data associated with medical encounters related to CAP or treatment (e.g., intubation, placement of chest tubes, tracheostomy) will be collected in the CRF by the investigator staff for all subjects. Protocol mandated procedures, tests, and encounters are excluded. These data will be used to conduct exploratory economic analyses.

Specifically, data collected will include:

- Number and duration of medical care encounters
- Duration of hospitalization
- Duration of hospitalization in ICU setting
- Number and character of diagnostic and therapeutic tests and procedures
- Concomitant medications

## **10. SUBJECT COMPLETION/WITHDRAWAL**

### **10.1. Completion**

A subject will be considered as having completed the study if he/she has completed all assessments at the LFU visit and received at least 5 days of study treatment. Subjects who discontinue study treatment after 48 hours of treatment due to lack of efficacy are also considered to have completed the study.

### **10.2. Discontinuation of Treatment**

A subject should be discontinued from study treatment if:

- the investigator believes that for safety reasons (e.g., adverse event) it is in the best interest of the subject to stop treatment
- the subject becomes pregnant
- creatinine clearance is <10 mL/min or the subject requires dialysis
- significant myelosuppression occurs during therapy with linezolid/placebo; treatment with linezolid/placebo should be stopped unless it is considered absolutely necessary to continue therapy, in which case, intensive monitoring of blood counts and appropriate management strategies should be implemented
- optic or peripheral neuropathy occurs during therapy with linezolid/placebo; treatment with linezolid/placebo should be stopped

unless it is considered absolutely necessary to continue therapy. Optic and peripheral neuropathy are potential adverse effects of linezolid therapy. Subjects will be educated on symptoms associated with optic neuropathy (e.g., acute blurred vision, vision loss, color loss) and peripheral neuropathy (e.g., paresthesia, sensory loss) and instructed to report them if they occur. If subjects report symptoms of visual impairment, such as changes in visual acuity, changes in color vision, blurred vision, or visual field defect, prompt ophthalmic evaluation is recommended. Visual function should be monitored in all subjects reporting new visual symptoms, regardless of the length of linezolid therapy. Subjects with significant or progressive symptoms will be discontinued from linezolid/placebo therapy and referred for specialty evaluation if symptoms persist.

If a subject discontinues treatment early, TOC assessments should be performed at the time of study drug discontinuation. The subject should be contacted at the LFU visit to obtain MRU information and to follow up on any ongoing adverse events.

